| Study Date Range and Duration
December 2024 – August 2026                                                                                                                                                                                                                                                                                                                  |
| Number of Study Sites
Yale New Haven Hospital                                                                                                                                                                                                                                                                                                                              |
| Primary Outcome Variables
We will use direct patient evaluation by pelvic floor therapists, a validated system usability survey to evaluate the ease of use of the web-based platform containing PFMT videos and monitor for adverse events.                                                                                                                               |
| Secondary and Exploratory Outcome Variables (if applicable)
Short Form 12 score, Cleveland Clinic Incontinence Score (CCIS), Patient Assessment of Constipation Symptoms (PAC-SYM), International Consultation on Incontinence Questionnaire Short Form (ICIQ-SF), and Pelvic Organ Prolapse Symptom Score (POP-SS) to assess improvement in symptoms and quality of life. |
| Study Population
Study population will include patients who have an indication for referral for pelvic floor rehabilitation (PFR).                                                                                                                                                                                                                                         |
| Number of Participants                                                                                                                                                                                                                                                                                                                                                        |

We plan to enroll 10-20 patients. This is a pilot study aimed at assessing feasibility, so this sample size is similar to other feasibility trials.

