# 1 Background/Literature Review

## 1.1 Background

Pelvic floor rehabilitation (PFR) is a group of therapeutic techniques used to help patients with pelvic floor dysfunction, such as urinary incontinence or fecal incontinence. The exercises commonly use in PFR include pelvic floor muscle therapy (PFMT) with biofeedback training, rectal balloon training or electrical stimulation. Together, these techniques aim to improve the strength, tone and endurance of the pelvic floor musculature and sphincter complex. For fecal incontinence, they have shown to decrease symptoms ranging between 50-80%. A meta-analysis looking at 18 trials utilizing PFMT for urinary incontinence found an improvement in symptoms in all studies.

Despite PFMT being shown to be efficacious for numerous different pelvic floor dysfunction disorders, less than 50% of patients referred are compliant with the recommend duration of treatment. Previous studies found that inconvenience, cost, lack of knowledge and discomfort around the concept of PFMT are all reasons why patients may have poor compliance. Patients have shown a positive reception to telehealth-based PFMT visits. It is not known if a hybrid approach to PFMT including both in-person and video-based training videos may help to alleviate some of these barriers while providing the same adequate amount of guidance, improvement in symptoms and QoL for patients. Thus, the purpose of this study is to evaluate the feasibility and acceptability of a web-accessible 8-week video-based PFMT for pelvic floor disorders.

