**3.2 Primary Objective**

The primary objective is to determine the feasibility and accessibility of using a video-based PFMT for patients with pelvic floor dysfunction.

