## 4.2 Outcome Variables

### 4.2.1 Primary Outcome Variables

SUS, percentage of video completion, change in the graded evaluation of exercises by pelvic floor therapist pre and post intervention, adverse events

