### 4.3.2 Eligibility Criteria/Vulnerable Populations

Eligibility will be assessed by a member of the study team reviewing outpatient clinic visits to colorectal surgery and urogynecology clinics at Yale New Haven Hospital and its associated ancillary clinic sites.

In order to be eligible for inclusion in this study, an individual must meet all of the following criteria:

1. Diagnosis of one of the five following diagnoses with referral for PFR
  - a. Urinary incontinence
  - b. Pelvic pain
  - c. Fecal incontinence
  - d. Postpartum-related symptoms
  - e. Constipation
2. 18 years or older
3. English-speaking
4. Access to internet

Vulnerable populations: none

Exclusion criteria:

1. Unable to access web-based videos
2. Unable to speak English

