## 5.4 Statistical Method

### 5.4.1 Statistical Design

Demographic information will be reported using descriptive statistics. Categorical variables will be analyzed with chi-squared test and continuous variables will be analyzed with Wilcoxon Rank sum test. Paired T-test will be used to evaluate differences pre and post treatment of the following measures:

- 1) amount of supervision and cues needed by the pelvic floor therapist
- 2) difference in graded scoring of exercises by the pelvic floor therapist
- 3) CCIS scores
- 4) PAC-SYM score
- 5) SF-12 Scores
- 6) ICIQ-SF Scores
- 7) POP-SS Scores

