### 5.4.3 Planned Analyses

The primary analysis to evaluate for feasibility and safety will involve the percentage of patients who successfully learned PFMT, analysis of incidence of adverse events and overall score of usability for the web-based videos. We will also evaluate the ability of participants to successfully complete the exercises based on the graded scoring by the pelvic floor therapists. Analysis of secondary outcomes

related to symptom improvement and quality of life will analyze SF-12, CCIS, PAC-SYM, ICIQ-SF and POP-SS scores.

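### The primary measures are stated inconsistently across sections, and the plan's own exclusion rule confines video completion to 75-100%

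*Protocol*

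**What the plan says.** The Protocol states its primary measures in four places.

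- Section 4.2.1 gives the formal list: "SUS, percentage of video completion, change in the graded evaluation of exercises by pelvic floor therapist pre and post intervention, adverse events".
- The Synopsis names three: "We will use direct patient evaluation by pelvic floor therapists, a validated system usability survey", followed by monitoring for adverse events.
- Section 5.1.1 also names three: adequacy of the therapy as judged by the therapists, usability of the video application, and adverse events.
- Section 5.4.3 describes the primary analysis as the "percentage of patients who successfully learned PFMT, analysis of incidence of adverse events and overall score of usability for the web-based videos", and then adds: "We will also evaluate the ability of participants to successfully complete the exercises based on the graded scoring by the pelvic floor therapists".

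Three further places bear on these. Section 5.3.3 has the therapist grade exercises from 1 (cannot replicate) through 2 (partial) to 3 (full) at the first and last in-person visits. Section 5.4.6 excludes from the study anyone who completes less than 75% of the videos or misses either in-person visit. Section 5.4.1 puts first among its paired t-tests the "amount of supervision and cues needed by the pelvic floor therapist".

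**The concern.** A feasibility pilot with 10-20 patients rests almost entirely on its primary descriptive measures, so these need to be the same wherever they are named. Here three things do not line up.

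First, video completion is primary in one section and absent from the other three. Its only analytic use is as a filter on who is analysed, and that filter removes the low values the outcome would need in order to show that the programme is hard to complete.

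Second, the outcome list has a change in grade, while the primary analysis leads with a percentage who learned. These are different quantities, and the Protocol does not say which is primary.

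Third, a pre/post test is listed for a measure that the visit schedule does not collect.

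At stake is whether the report can say clearly that the programme was, or was not, feasible.

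**Working it through.** The plan has no figure of its own to reproduce here: it sets no feasibility threshold, and the 10-20 sample size is justified only by similarity to earlier feasibility studies. The check is a comparison of sections, with arithmetic on invented data to show scale.

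**1. The four statements side by side**

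| Measure | Synopsis | 4.2.1 | 5.1.1 | 5.4.3 |
|---|---|---|---|---|
| Usability | yes | yes | yes | yes |
| Adverse events | yes | yes | yes | yes |
| Therapist assessment | direct evaluation | pre/post change in grade | adequacy | percentage who learned; ability by graded scoring |
| Video completion | no | yes | no | no |

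The first two rows agree. The conflict is confined to the last two.

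**2. Grade attained against grade change**

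Illustration (assumed data, one grade per patient, 20 patients): 8 stay at 3, 6 go from 2 to 3, 3 go from 1 to 2, 3 stay at 2.

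- Final grade 3: (8 + 6)/20 = 70%.
- Final grade 2 or 3: 20/20 = 100%.
- Improved by at least one grade: (6 + 3)/20 = 45%.
- Mean change: (6 × 1 + 3 × 1)/20 = 0.45. With 9 ones and 11 zeros, SD = √[(9 × 0.55² + 11 × 0.45²)/19] = 0.51 and t = 0.45/(0.51/√20) ≈ 3.9 on 19 df, p about 0.001.

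A second assumed set of ten patients: six stay at 3, two go from 2 to 3, two stay at 2. Final grade 3 is 8/10 = 80%, improved is 2/10 = 20%, and mean change is 2/10 = 0.2, with paired t = 1.50 on 9 df, p = 0.17.

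In both sets every reading is in the favourable direction; what changes is the size. The eight and six patients already at grade 3 are the reason: they have no room to improve, so they add nothing to change but count fully towards grade attained.

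**3. What section 5.4.6 does to video completion**

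Every analysed patient has completed between 75% and 100%, so the mean must also lie in that range, and the proportion reaching 75% is 100% by construction.

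Suppose 20 enrol and 10 are kept, the other 10 all being below 75% (an assumption; section 1.1 cites compliance under 50% for referred patients). Over all enrolled, the proportion reaching 75% is 10/20 = 50%. Mean completion could be as low as (10 × 75 + 10 × 0)/20 = 37.5%. Among those kept, the same programme shows 10/10 = 100% and a mean of at least 75%.

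**4. What it does to the percentage who learned**

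Under the same assumption, with 8 of the 10 kept graded as fully performing: 8/10 = 80% (exact 95% CI 44-98%) among those kept, but 8/20 = 40% (19-64%) among those enrolled. With 15 kept and 12 successes: 12/15 = 80% against 12/20 = 60%.

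**5. Supervision and cues**

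Section 5.3.3 itemises both therapist visits. The only scored item is the 1-3 grade, and section 5.2 likewise mentions only graded scoring. Supervision and cues is in no outcome list and at no visit.

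**The case against.** The strongest reply is that the disagreement is narrower than it first appears. Usability, adverse events and some form of therapist assessment are in all four statements, and section 5.4.3 does refer to the graded scoring in its next sentence. A cut-off for having learned is the kind of detail an analysis plan not shown here could supply. All of that stands. It does not settle whether the primary quantity is a level attained or a change, because the Protocol says one in 4.2.1 and leads with the other in 5.4.3.

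On supervision and cues, a reader might infer that the test cannot be run. The text does not go that far: section 5.1.1 puts the therapist's assessment in the database, section 6.4 mentions metrics of exercise performance, and the therapist's form is not shown. What stands is that the visit schedule does not list the item.

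A reader might also infer that accessibility cannot be observed, since section 4.3.2 excludes anyone "Unable to access web-based videos". The Protocol never defines accessibility as internet access. The barriers it describes in sections 1.1, 1.2 and 2.1 include waiting time, travel, inconvenience and cost, and an internet requirement does not hide those.

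On video completion, it may be said that the number excluded would be reported anyway. That may be so, but no planned analysis says it, and 5.4.6 excludes these patients from the study without exempting the completion outcome.

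**Conclusion.** The point holds as an inconsistency within the Protocol. Video completion is primary in 4.2.1 only, and under 5.4.6 it is confined to 75-100% in the analysed set, so it cannot show poor feasibility. The grade outcome is a change in 4.2.1 and an undefined percentage in 5.4.3; in the illustration the same patients give 45%, 70% or 100%, and a patient at grade 3 throughout could count as learned while showing no change. One listed t-test has no itemised data.

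The truncation follows directly from the text. The percentages rest on invented grades and assumed retention, and on one grade per patient where the Protocol grades several exercises; they show scale and predict nothing.

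Two stronger conclusions a reader might draw are not supported. The readings do not point in opposite directions: in both examples they agree in sign and differ in size. Nor does anything in the Protocol plan to pick the best-looking reading; the text merely leaves the choice open.

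A minor wording point remains. Section 3.2 aims to "determine the feasibility and accessibility of using a video-based PFMT for patients with pelvic floor dysfunction", and the Synopsis Purpose also says accessibility, while section 1.1 sets out to "evaluate the feasibility and acceptability of a web-accessible 8-week video-based PFMT".

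**What to change.** 1. Use one identical primary list in the Synopsis and in sections 4.2.1, 5.1.1 and 5.4.3.
2. Report video completion over all enrolled patients, both as the percentage completed and as the proportion reaching 75%, and not only in those kept by 5.4.6.
3. State whether the therapist-grade outcome is the final grade attained or the pre/post change. Tie having learned to the 1-3 scale over the exercises the patient did not opt out of, since section 2.3.1 allows opting out. Keep all enrolled as the denominator, and show a baseline-by-final grade table so that patients already at grade 3 are visible.
4. Either add supervision and cues to both therapist visits in 5.3.3 or delete the test from 5.4.1.
5. Align accessibility (Synopsis Purpose and 3.2) with acceptability (1.1), changing every place together.

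The cost is Protocol wording through an IRB-approved amendment, a few simple tables, and at most one extra item on the therapist's form. Visits, sample size and treatment are unchanged.

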#### **5.4.4 Analysis of Subject Characteristics (if applicable)**

We will analyze general demographic information such as age, sex, race, ethnicity.

#### **5.4.5 Interim Analysis (if applicable)**

#### **5.4.6 Handling of Missing Data**

Patients who complete less than 75% of the videos or do not attend both initial and final in person pelvic floor therapy visit will be excluded from the study. A complete case analysis will be performed for patients who have completed between 75-100% of the videos.

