### 5.4.2 Sample Size Considerations

This is a feasibility study with no prior literature publishing on the use of video-based PFMT. Based on prior feasibility studies, the sample size will be between 10-20 patients.

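### Section 5.4.6 selects the analysis set on video completion, a primary outcome, so reported completion cannot fall below 75% and other feasibility results lose those who stopped

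*Protocol*

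**What the plan says.** The primary objective in section 3.2 is stated as follows: "The primary objective is to determine the feasibility and accessibility of using a video-based PFMT for patients with pelvic floor dysfunction". Section 4.2.1 gives the primary outcomes as "SUS, percentage of video completion, change in the graded evaluation of exercises by pelvic floor therapist pre and post intervention, adverse events". Section 5.4.3 describes the primary analysis of feasibility and safety as "the percentage of patients who successfully learned PFMT, analysis of incidence of adverse events and overall score of usability for the web-based videos", together with the therapist's grading of the exercises.

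Section 5.4.6, under the heading for missing data, gives the rule for removing patients from the study: those that "complete less than 75% of the videos or do not attend both initial and final in person pelvic floor therapy visit will be excluded". It continues: "A complete case analysis will be performed for patients who have completed between 75-100% of the videos". No other analysis set is named anywhere in the protocol. There is no all-enrolled set and no safety set, and nothing says that excluded patients will be counted or described in any result.

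Sections 5.2 and 5.3.3 collect the SUS twice, at the midway check-in after 4 weeks and again with the closing surveys. On enrolment, section 5.4.2 says: "Based on prior feasibility studies, the sample size will be between 10-20 patients".

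**The concern.** In a feasibility study, stopping the videos or not returning for the final visit is a result. Section 5.4.6 treats it as missing data and removes it. The background in section 1.1 makes adherence the motivating problem, reporting that "less than 50% of patients referred are compliant with the recommend duration of treatment", yet the plan measures adherence only in those who adhered.

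The rule also discards data that will exist. A patient who watches 60% of the videos and attends both visits has two therapist grades. A patient who stops in week 6 may already have a midway SUS. Anyone who stops because of discomfort during unsupervised exercise, a risk that section 2.3.1 acknowledges, drops out of the adverse-event incidence. At stake is whether the reported figures describe the patients offered the programme or only those who finished it.

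**Working it through.** **What can be reproduced.** The protocol gives no power, dropout rate, feasibility threshold or other calculation behind the 10-20 patients, so there is no planned figure to reproduce. The check below does not depend on one.

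**Inputs.** From the protocol: the 75% cut-off and the two-visit condition (5.4.6), the primary outcomes (4.2.1, 5.4.3), and N = 10-20 (5.4.2). Assumed, because the protocol does not give them: the share retained (50% or 80%), completion and learning among the retained, and everything about those excluded.

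**1. Video completion.** Every analysed patient has completion of at least 75%, so the analysed mean is at least 75%. This needs no assumption. For size, take a mean of 90% among the retained and 10-50% among the excluded. The all-enrolled mean is r × 90 + (1 − r) × e, where r is the retained share and e the mean among the excluded.

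- r = 0.5: 0.5 × 90 + 0.5 × 10 = 50%, up to 0.5 × 90 + 0.5 × 50 = 70%. The rule reports 90%.
- r = 0.8: 0.8 × 90 + 0.2 × 10 = 74%, up to 0.8 × 90 + 0.2 × 50 = 82%. The rule reports 90%.

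**2. Percentage who learned.** With L learners among R retained out of N enrolled, the rule reports L/R. If no excluded patient learned, the all-enrolled figure is L/N, so the inflation factor is N/R. Exact (Clopper-Pearson) 95% intervals with N = 20:

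| Retained | Learned | Under the rule | All enrolled | Factor |
|---|---|---|---|---|
| 10 (50%) | 9 | 9/10 = 90% (55-100%) | 9/20 = 45% (23-68%) | 20/10 = 2.0 |
| 16 (80%) | 14 | 14/16 = 88% (62-98%) | 14/20 = 70% (46-88%) | 20/16 = 1.25 |

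These are the largest gaps for the given L and R. If excluded patients learned at the same rate as the retained, the gap closes: in the first row, 9 of the 10 excluded also learning gives (9 + 9)/20 = 90%.

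**3. Adverse events.** Assume 5% incidence in the retained and 5-30% in the excluded. All-enrolled incidence at r = 0.5 runs from 5% to 0.5 × 5 + 0.5 × 30 = 17.5%. At r = 0.8 it runs from 5% to 0.8 × 5 + 0.2 × 30 = 10%. The rule reports 5% throughout. With equal incidence there is no bias. The same reasoning applies to SUS.

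**4. Will the rule operate?** If each patient independently has an 80% chance of being retained, the probability that nobody is excluded is 0.8^10 = 0.11 with 10 enrolled and 0.8^20 = 0.01 with 20.

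**The case against.** Several points on the other side stand.

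- **Only completion is affected by construction.** Learning is inflated only if non-completers learned less. SUS and adverse events are biased only if non-completers differ.
- **Video completion is unevenly specified.** It is a primary outcome in 4.2.1 but is absent from the Synopsis outcomes, from the comparison described in 5.1.1 and from the primary analysis in 5.4.3. The outcome that is strictly truncated is thus not in the primary analysis as written. That is a further inconsistency to resolve and does not excuse the rule.
- **Pre/post grade change needs both visits.** Restricting paired comparisons to patients with both measurements is ordinary practice, so removing the exclusion altogether would go too far.
- **Safety oversight is intact.** Section 5.1.2 gives every patient a contact route and sets event reporting with no completion condition. Only the analysed incidence is affected.
- **The under-50% compliance figure is a weak benchmark.** It concerns patients referred for therapy in cited literature, not consented participants paid for attending visits in a video programme. It does not predict retention here.
- **The visit condition is ambiguous.** It can mean missing either visit or missing both. On the narrower reading fewer patients are excluded, but the 75% cut-off still applies.

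A reader might infer that the trial cannot produce a negative feasibility result, or that its primary objective goes unanswered. The protocol does not support either. Low SUS scores, poor grades or a low percentage learned could still appear among completers, and no success threshold for completion is stated. Nor can the matter be left to an analysis plan that is not shown, because the protocol itself fixes the rule.

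**Conclusion.** The rule is wrong as written. For video completion, the 75% floor follows from the text alone. For the percentage who learned, the overstatement is up to a factor of 2.0 at 50% retention and 1.25 at 80%, on the assumption that excluded patients did not learn, and it shrinks as more of them did. For SUS and adverse events, a too-favourable result is likely, conditional on those who stop differing from those who finish. The retention shares and the rates among excluded patients are illustrations. A set limited to 75-100% completion is legitimate as a supportive analysis; the defect is that it is the only set named.

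**What to change.** Amend 5.4.6 and 5.4.3 as follows.

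- Report video completion, visit attendance and the percentage who learned over all enrolled participants. Count those without a final assessment as not shown to have learned, and give the assessed-only figure alongside.
- Report adverse events in all who started a session, and SUS, including the midway score, in all who answered.
- Make the proportion who complete at least 75% of videos and attend both visits a feasibility endpoint with an exact 95% CI. The interval will be wide (16/20 gives 56-94%, 8/10 gives 44-97%), so it should be read descriptively.
- Add video completion to the primary analysis in 5.4.3 so that it matches 4.2.1, and state whether missing one visit is enough to fail the attendance condition.
- Keep pre/post comparisons to those with both measurements, and keep the 75-100% group as a labelled supportive analysis.

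The cost is an IRB-approved amendment before implementation (sections 6.2 and 6.10), closing surveys sent to non-completers, and probably less favourable feasibility figures.
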